### Secondary outcomes for effectiveness evaluation

***Health-related quality of life ***will be measured with the Assessment of Quality of Life-6D (AQoL-6D) scale, which is composed of six domains (independent living, relationships, mental health, coping, pain, senses) [75]. The AQoL-6D has response scales that include 4–6 levels for each item, with higher scores indicating quality of life impairment. At baseline, the online survey included additional information for those still receiving inpatient treatment (“*For some questions, please imagine that you would have been at home if you are currently in the hospital*.”).

***Mental functioning*** will be measured with the 7-item Managing-scale and 6-item Cooperation/Communication scale from the Norwegian Function Assessment Scale (NFAS) [76]. The NFAS has a 5-point response scale, ranging from 1 (*no difficulty*) to 5 (*could not do it*). In accordance with [76], a response category item ‘*inapplicable to me, task not performed*’ was added and recorded as missing. The two NFAS subscale scores are each computed by calculating a mean score of the completed items, with low scores indicating good mental functioning [77].

***Overall job satisfaction*** will be measured with the following single-item question of the Job Satisfaction scale from the Copenhagen Psychosocial Questionnaire (COPSOQ) [78]: “*Regarding your work in general. How pleased are you with your job as a whole, everything taken into consideration?*” The single-item question has a 5-point response scale, with the answer options: *very satisfied*, *satisfied*, *unsatisfied*, *very unsatisfied*, and *not relevant*. However, we deleted the last response option and added ’*partly*’ as a third response option in between the scale to enable participants to respond neutrally to the question without forcing an answer in the positive or negative direction. The score of the single-item question ranges from 100 to 0, with higher scores indicating more job satisfaction.

***RTW self-efficacy*** will be assessed with the RTW self-efficacy scale (RTW-SE) [79], which was translated and verified in an earlier study [80]. The RTW-SE includes 11 items and has a 6-point response scale, ranging from 1 (*totally disagree*) to 6 (*totally agree*). A mean score over all 11 items is used to compute a total RTW-SE scale score, with higher scores indicating higher perceived self-efficacy regarding RTW.

***Severity of mental illness*** will be measured with three 6-item scales (somatisation, depression, anxiety) from the Brief Symptom Inventory-18 (BSI-18) [81]. The BSI-18 has a 5-point response scale, ranging from 0 (*not at all*) to 4 (*extremely*). The scores on each of the three BSI-18 scales range from 0 to 24. The sum score of the BSI-18, referred to as the Global Severity Index, ranges from 0 to 72, with higher scores indicating more distress [82].

***Work ability*** Will be measured with the single-item Work Ability Score (WAS) [83]. The WAS has an 11-point response scale, ranging from 0 (*completely unable to work*) to 10 (*lifetime´s best work ability*).

### Key outcomes for health-economic evaluation

#### Health-related outcomes

In the cost-effectiveness analysis, the main outcome will be the employees´ achievement of SRTW (yes/no). In the cost-utility analysis, quality-adjusted life years (QALYs), based on the AQoL-6D, will be the health-related outcome. The AQoL-6D generates patient preference-based utilities on a scale of 0 (death) to 1 (perfect health), using the time-trade-off method [84]. QALY gains will be estimated by calculating the area under the curve of linearly interpolated AQoL-6D utility values between assessment points to cover the follow-up period.

#### Cost measures

Costs will be measured from the societal, public health care and employer's perspectives. In the societal perspective, all costs related to the interventions (i.e. health care, patient and family and productivity costs) will be taken into account irrespective of who pays or benefits. Using the public health care perspective, only intervention and health care costs will be considered. When applying the employer's perspective, only costs and economic benefits pertinent to employers will be included (i.e. productivity costs) plus intervention costs, assuming that the latter would be paid for by the employer. For this, the TiC-P [73, 74], a retrospective questionnaire with a 3-month recall period and specifically adapted to patients of POCs, will be applied to collect data on health care use, patient and family costs, and productivity costs. Calculation of health care costs will be based on two German guidelines [85, 86].

### Further variables

The following variables will be predominantly used as possible outcomes, covariates, moderators, or mediators within further exploratory analyses.

***Depressive symptoms*** will be measured with the Patient Health Questionnaire (PHQ-9) [87]. The PHQ-9 has a 4-point response scale, ranging from 0 (*not at all)* to 3 (*nearly every day*). The sum score ranges from 0 to 27, with higher scores indicating the severity of depressive symptoms.

***Interpersonal trust*** will be measured with the Interpersonal Trust Short Scale (KUSIV3) [88]. The KUSIV3 has a 5-point response scale, ranging from 1 (*do not agree at all*) to 5 (*completely agree*). The sum score ranges from 3 to 15, with higher scores indicating higher interpersonal trust.

***RTW expectation*** will be assessed with a single-item from the Screening Instrument Work and Occupation (SIBAR) [89]. The question was slightly adapted with respect to the study-specific setting at baseline (*“Considering your current state of health, when do you think you will be able to return to work after your discharge?”*). The SIBAR has a 7-point response scale, with the answer options: *immediately*, *one month*, *three months*, *six months*, *nine months*, *one year or later*, and *not at all anymore*. As has been done before [90], the single SIBAR-item responses will be dichotomised into a’positive RTW expectation (≤ 3 months)’ and’negative RTW expectation (> 3 months)’.

***Social support*** will be measured with the brief version of the Perceived Social Support Questionnaire (F-SozU K-6) [91]. The F-SozU K-6 has a 5-point response scale, ranging from 1 (*not true at all*) to 5 (*very true*). The sum score ranges from 6 to 30, with higher scores indicating higher levels of general perceived social support.

***Socio-demographics*** will be assessed at baseline (T0) with several items including information on *gender*, *age, education, marital status, cohabitation, residence, total number of inhabitants of the place of residence* (extra item asking for the *number of inhabitants younger than 14 years*) [92], *occupational status, company sector, monthly gross household income* [73]*, degree of disability* [89]*, ethnicity, migration* [93] and *distance to the practice of the respective therapist or other practitioners* [73]. Data on *household income* will be collected at all five measurement points for the health-economic evaluation.

***Treatment satisfaction*** with the overall RTW-PIA treatment as well as with each RTW-PIA module (A-C) will be assessed with an adapted version of the Questionnaire for Patient Satisfaction (ZUF-8) [94]. The ZUF-8 has a 4-point response scale, ranging from 1 (*does not apply to me*) to 4 (*does totally apply to me*). The response category ‘*inapplicable to me, I did not participate’* was added to the scale to prevent socially desirable answers; scoring this answering category means that data are missing for the reason that the persons did not participate. In addition, the questions were slightly adapted with respect to the specific module (e.g. “*Please indicate the extent to which the following statements about Module B apply to you*”; (1) “*The group discussions I have participated in have so far been of high quality*”). As has been done before, the questions were rephrased as statements in order to have constant response categories within the ZUF-8 scale [95]. The sum score of the ZUF-8 ranges from 8 to 32 points, with higher scores indicating more treatment satisfaction.

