### *Recruitment procedure*

Patients who currently receive inpatient, day-care, or outpatient treatment in psychiatric clinics or POCs are screened for eligibility by the trained treatment teams of the respective study centres. A flowchart of the recruitment procedure and the study participants’ progress is shown in Fig. 1. Prior to study inclusion, all potentially eligible patients identified for the study will be invited to the one-time enrolment module “Work and Health”, which includes a psychoeducational group session on the following topics: interdependency of health and work, significance of work and its potential positive and negative effects, occupational integration management, and gradual RTW. At the end of the enrolment module, patients are informed about RTW-PIA and asked about their willingness to participate. Patients who give their written informed consent are then invited to the online baseline assessment. After successful completion of the baseline assessment, the patients are randomised to the IG or CG. The recruitment process started in September 2021.

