#### *Statistical analyses*

### Effectiveness evaluation

The primary outcome will be analysed using a logistic regression model to determine the odds ratio of the intervention effect. First, we will estimate a baseline model including treatment group (IG vs. CG) as a dummy-coded predictor variable and SRTW achievement as the outcome variable. Second, we will compute an adjusted estimate by including the stratification variable of the study centres as well as, if necessary, other socio-demographic variables for which differences between IG and CG occurred despite randomisation. Weighted effect coding will be considered for study centre, using the largest group as the reference group. Third, we will explore interaction effects between treatment group and all baseline assessments of the secondary outcomes and further variables. In case of statistically significant interaction effects, we will report intervention effects for different values of the covariates. In these and subsequent models, we will adopt a significance level of 5% for testing the focal parameters and report corresponding 95% confidence intervals (CIs).

In the context of the secondary analysis, multiple-group latent growth curve models (LGCM) will be estimated to investigate the effect of the intervention on changes in health-related quality of life, mental functioning, overall job satisfaction, severity of mental illness and work ability. LGCM are based on a structural equation modelling framework and allow for a more flexible adaptation to the specifics of the data structure than many multilevel models [100]. For each secondary outcome variable, we will include data at five time points and estimate a multiple group latent-basis model. This model is a less restrictive variant of the linear growth curve model, i.e. it contains a latent intercept for baseline differences and a latent slope for change differences, but can also represent nonlinear forms of change. If necessary, we will allow the residual variances to differ between treatment groups and time points. The focal parameter in each model is the mean difference of the latent slopes between treatment groups.

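### Return-to-work expectation is timed from discharge in a sample that includes outpatients, and its seven ordered answers are cut to two; this weakens exploratory analyses only and is cheap to improve

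*Protocol article*

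**What the plan says.** Under *Further variables*, the protocol article measures RTW expectation with one item, adapted for baseline to read "Considering your current state of health, when do you think you will be able to return to work after your discharge". It continues: "The SIBAR has a 7-point response scale, with the answer options", and lists immediately, one month, three months, six months, nine months, one year or later, and not at all anymore. For analysis, "the single SIBAR-item responses will be dichotomised into a’positive RTW expectation (≤ 3 months)’ and’negative RTW expectation (> 3 months". The reason given is precedent: "As has been done before [90" introduces the rule by citation.

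Under *Recruitment procedure*, "Patients who currently receive inpatient, day-care, or outpatient treatment in psychiatric clinics or POCs are screened for eligibility". Under *Secondary outcomes for effectiveness evaluation*, the quality-of-life questionnaire carries "additional information for those still receiving inpatient treatment" at baseline. The article describes nothing similar for the expectation item.

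On use, the opening of *Further variables* assigns these measures mainly to exploratory work, as possible outcomes, covariates, moderators or mediators. In *Effectiveness evaluation* (statistical analyses), the primary outcome is modelled in three steps, and the item comes in at the last: "Third, we will explore interaction effects between treatment group and all baseline assessments of the secondary outcomes and further variables". The same section explores baseline variables as predictors of change in the secondary outcomes. It also brings baseline variables that predict missingness into the estimation, through multiple imputation for the primary outcome.

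**The concern.** Two features of one variable combine.

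The first is the anchor. For an inpatient, discharge is a future date that differs from person to person. For someone already in outpatient care it is either undefined or taken as the end of some treatment. All follow-up surveys run from completion of the baseline survey, so the same answer can stand for different times on the trial's own clock.

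The second is the cut. Someone who expects to be able to work in six months, well inside the 24-month follow-up, is placed with someone who expects never to return. Any shift in time origin that crosses three months becomes a complete change of class.

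At stake is the precision of the treatment-by-expectation test, the detail with which an interaction could be reported (a split allows two values only), and the usefulness of the item in adjustment and imputation.

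**Working it through.** **What does not depend on this item.** The document gives no figure for the item. Its nearest figure is the sample size: 60% against 75%, 80% power, 5% level. Taking the level as two-sided, with mean proportion 0.675:

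n = [1.960·√(2·0.675·0.325) + 0.842·√(0.60·0.40 + 0.75·0.25)]² / 0.15² = (1.298 + 0.550)² / 0.0225 ≈ 152 per arm, as stated.

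No covariate enters this formula, so the item has no bearing on it. Steps one and two of the primary model contain treatment, then centre and, if necessary, unbalanced socio-demographic variables. RTW expectation is listed separately from the socio-demographics and first appears in step three.

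**Time origin, worked as an illustration.** Suppose an inpatient has two months of stay left (assumed) and answers three months. The expected return is 2 + 3 = 5 months after baseline, coded positive. An outpatient who also expects five months and picks six months, the nearer option, is coded negative. The two have the same expected return and opposite codes. How often this happens cannot be calculated: the mix of settings, the remaining stay and the answer distribution are not in the document.

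**Information kept by the split.** For a linear effect of a score s, the two-level version keeps the fraction

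r² = p(1−p)·(m₂ − m₁)² / Var(s),

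where p is the share answering three months or less, and m₁ and m₂ are the mean scores below and above the cut. With scores 1 to 7 and assumed answer shares:

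- Equal shares: p = 3/7, m₁ = 2, m₂ = 5.5, Var = 4. r² = (12/49)·12.25/4 = 0.750; loss 25%.
- 10/20/30/20/8/9/3%: p = 0.60, m₁ = 2.333, m₂ = 4.875, Var = 2.2875. r² = 0.24·6.460/2.2875 = 0.678; loss 32%.
- 5/25/35/20/5/7/3%: p = 0.65, m₁ = 2.462, m₂ = 4.800, Var = 1.8816. r² = 0.2275·5.468/1.8816 = 0.661; loss 34%.

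**How far this moves under other assumptions.**

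- Rounded-normal answers with 37% to 63% positive: loss about 28% to 34%.
- Underlying normal variable, r² = φ(z)²/[q(1−q)] with q the share positive: loss 36% at 50/50, 42% at 30/70, 51% at 20/80, 66% at 10/90.
- Polarised answers, for example 35/10/3/2/5/20/25%: loss about 7%; a milder two-peaked pattern, 25/20/10/5/10/20/10%: about 15%.
- Scores in months (0, 1, 3, 6, 9, 12, with the last answer set to 18 or 24): loss about 13% to 62% over nine assumed distributions.
- Very uneven splits can lose slightly more than this range: a rounded-normal case with only 7% positive loses 70%.
- A true step at three months: essentially no loss.

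**In participants.** The plan targets 2 × 152 = 304 analysable participants. A loss of 25% to 34% leaves the precision of about 304·0.75 = 228 down to 304·0.66 ≈ 201 participants for a linear effect of this item.

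**The case against.** The strongest reply is that the variable hardly matters to the trial's main claim. It is labelled exploratory, appears in neither of the first two steps of the primary model, and plays no part in the sample size. That stands and sets the weight of the point. A reader might infer that mixed time origins bias the treatment comparison. They do not: the item is answered before allocation, so randomisation spreads the ambiguity over both arms, and what remains is noise in one covariate or moderator.

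Second, the cut follows a cited study that cannot be inspected here and may justify it. That is a reason to keep the split for comparison, not a reason to discard the seven collected answers in the models.

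Third, the article is condensed, appears to give an English rendering of a survey aimed at German-speaking participants, and refers to an additional file that is not shown. A variant for outpatients may exist. The time-origin point therefore applies to the wording printed, and no more.

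Fourth, a reader might take a quarter to a third as this trial's actual loss. The document gives no answer distribution, the options are unevenly spaced in time, and the last option is not a time at all, so no single figure can be claimed. Nor is it shown that misclassification is worst at the three-month cut.

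Finally, patients who have decided against returning are excluded, so the extreme answer may be rare. The item asks about ability rather than decision, however, so the answer need not be absent.

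**Conclusion.** The point holds as a cheap improvement. The printed item ties its time scale to an event that not all recruited participants share, and the planned cut removes the order within each half of a seven-level answer on precedent alone. The consequences are confined to the step-three moderator analysis, the predictor analyses and possibly the missing-data model.

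For a linear effect, the loss is about 25% to 34% if answers are near-balanced and scores equally spaced. It is about 7% to 66% over the other main assumptions tried, and close to nothing if expectation truly acts as a threshold near three months. These figures rest on assumed distributions and exclude any misclassification from the time origin, which cannot be quantified. The document supports no conclusion that the unadjusted or centre-adjusted primary estimate, or the sample size, is affected.

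**What to change.** In the analysis plan that the protocol says will be registered before database closure:

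- Enter the seven-level response as ordered, either as a score or as an ordinal factor, in the moderator, covariate and imputation models, and state the scoring in advance.
- Keep the split at three months for describing the sample and for comparison with the earlier study.
- Include baseline treatment setting (inpatient, day-care, outpatient) alongside the item where it is recorded. This can absorb average differences between settings, but not differences in remaining stay within a setting.
- Report the discharge anchor as a limitation.

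A reader might want to re-anchor the question to the survey date for later enrollees. Recruitment began in September 2021, so that would put two time origins into one variable and add to the problem. The wording should stay as it is.

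The cost is a few lines of the analysis plan and no new data collection. Comparability with the earlier study becomes slightly less direct in the models, and the descriptive split preserves it.

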### Job characteristics and RTW-related measures

Throughout the five online assessments (T0-T4), participants will be asked to answer questions related to job characteristics (self-developed and [96, 97]) so as to continuously capture their current working status (*contractually agreed weekly work hours and working days/week, thoughts of workplace shift, actual (internal) workplace shift, job loss experience,* etc.) and to assess possible adaptions/changes with regard to their unique employment contract details. Further information will be assessed with regard to RTW (e.g. *RTW to previous business (yes/no)*; *RTW to previous workplace (yes/no)* (if not applicable, *reason for company change* and *date*)), gradual RTW and the workplace integration management process. The paper by Sikora et al. [80] served as orientation for designing the questions.

#### Sample size and power calculation

In order to demonstrate a 15% increase in the proportion of employees from the IG achieving SRTW, based on [80] (CAU: 60%; RTW-PIA: 75%; power: 80%; significance level: 5%), the required sample size will be a minimum of 152 study participants per study arm. Calculations were performed with a sample size software [98]. Following previous authors [58, 99], we assumed a drop-out rate of 40%; thus, 506 participants will be needed in total.

#### *Statistical analyses*

### Effectiveness evaluation

The primary outcome will be analysed using a logistic regression model to determine the odds ratio of the intervention effect. First, we will estimate a baseline model including treatment group (IG vs. CG) as a dummy-coded predictor variable and SRTW achievement as the outcome variable. Second, we will compute an adjusted estimate by including the stratification variable of the study centres as well as, if necessary, other socio-demographic variables for which differences between IG and CG occurred despite randomisation. Weighted effect coding will be considered for study centre, using the largest group as the reference group. Third, we will explore interaction effects between treatment group and all baseline assessments of the secondary outcomes and further variables. In case of statistically significant interaction effects, we will report intervention effects for different values of the covariates. In these and subsequent models, we will adopt a significance level of 5% for testing the focal parameters and report corresponding 95% confidence intervals (CIs).

In the context of the secondary analysis, multiple-group latent growth curve models (LGCM) will be estimated to investigate the effect of the intervention on changes in health-related quality of life, mental functioning, overall job satisfaction, severity of mental illness and work ability. LGCM are based on a structural equation modelling framework and allow for a more flexible adaptation to the specifics of the data structure than many multilevel models [100]. For each secondary outcome variable, we will include data at five time points and estimate a multiple group latent-basis model. This model is a less restrictive variant of the linear growth curve model, i.e. it contains a latent intercept for baseline differences and a latent slope for change differences, but can also represent nonlinear forms of change. If necessary, we will allow the residual variances to differ between treatment groups and time points. The focal parameter in each model is the mean difference of the latent slopes between treatment groups.

In addition, we will explore several baseline variables as prognostic and prescriptive predictors of change. To do this, we will use the EffectLiteR approach and consider baseline variables in the multiple-group LGCM [101]. The focal test for potential prescriptive variables is an omnibus test for interactions between treatment group and baseline variables. All model parameters are estimated using full information maximum likelihood. To account for possible deviations from a normal distribution in outcome variables, we use scaled test statistics and robust standard errors.

All data will be analysed according to the intention-to-treat principle. Missing data for the primary and secondary outcomes are assumed to be “missing at random” (i.e. missing at random conditional on information from all variables included in the respective model). To make this assumption plausible, we will first correlate all baseline variables with the missingness of data at later time points, and then include all baseline variables that predict missingness in the estimation of focal parameters. For the analysis of the primary outcome, we will implement this using multiple imputation by chained equations (MICE) [102]. For the analyses of the secondary outcomes, we will use an auxiliary variables approach [103].

A per-protocol approach for the following two pre-defined IG subgroups will be conducted as sensitivity analyses: (1) for those who had attended at least 3 out of 8 Module A sessions, 6 out of 9 Module B sessions, as well as 1 out of 3 video call session(s) within Module C; and (2) for those who have provided their data at all measurement time assessments (T0-T4). Another sensitivity analysis will be conducted to investigate different diagnostic patient subgroups (e.g. CMDs (F3, F4) vs. all others).

Further details of the statistical analyses will be determined in an analysis plan, which will be pre-registered via the Open Science Framework [104] before database closure. Additional quality assurance and monitoring by an independent statistical expert will be considered throughout the project period. All effectiveness evaluation analyses will be performed using the statistical platform R 4.1 or higher.

